## Justification of Dosing

### Justification of 0, 1, and 2 Month Dosing

The Phase I trials in Kombewa Division, Kenya, Mal-024 (40 adults) and Mal-031 (135 children) both used a 0, 1, 2 month schedule. This schedule is compatible with incorporation into the World Health Organisation’s Expanded Programme of Immunisations (EPI) and thus is relevant to our plans for further development of the vaccine in pediatric populations.

For justification of the 0, 1, and 2 month dosing of the comparator vaccine, see Section 3.7.

### Justification of the 50 µg Dose

Preliminary data from Mal-031 indicate no increased incidence of adverse events associated with the 50 µg dose compared to the lower doses. Moreover, approximately 80% of study subjects receiving the 50 µg dose achieved a four-fold or greater rise in anti-FMP1 titer at study day 90 (i.e., 30 days after the third vaccination), a percentage higher than either the 10 or 25 µg dose. The 50 µg dose gave a 16-fold increase in the GMT of the anti-FMP1 antibody titers in most children. The assumption that vaccine efficacy will increase with level of antibody titer (a surrogate marker) has led us to select the high (50 µg) dose for further evaluation (see Section 3.5.2).

## Comparison Vaccine

### The Vaccine

A rabies vaccine (either *Imovax*® [HDCV rabies vaccine] or (*Rabipur*®/*RabAvert*® [PCEC rabies vaccine]) will serve as the comparator in this study. The recommended doses and schedules are the same for infants, children, and adults (see Section 9.2 for more details). Rabies vaccine is a parenteral preparation of inactivated rabies virus used to promote active immunity to rabies in individuals exposed to the disease or virus. Prophylactic doses of rabies vaccine are administered to certain groups of people at high risk for acquiring rabies infection. Advantages of providing pre-exposure vaccination include reduced number of doses of the vaccine after a rabies exposure, elimination of need for rabies immune globulin post-exposure, possible protection in persons whose post-exposure therapy is delayed or unavailable, and possible protection for persons at risk for inapparent exposures to rabies. Pre-exposure vaccine is recommended for individuals at risk of occupational exposure to the rabies virus (e.g., physicians, veterinarians, laboratory workers, animal handlers). Pre‑exposure vaccination is also recommended for other persons whose activities involve frequent contact with rabies virus or potentially rabid animals such as bats, raccoons, skunks, cats, or dogs. Pre-exposure vaccination is commonly recommended in international travelers who are likely to come in contact with animals in areas where dog rabies is enzootic and immediate access to appropriate medical care, including biologics, might be limited. In our study area, as throughout Kenya (18), most people are at risk for dog and cats bites, but are rarely vaccinated against rabies. Since rabies vaccine is not widely available in the public health facilities, provision of the product is of great benefit to the study participants.

The 200 comparison subjects will receive this comparator vaccine during the active phase of the study; it will also be offered free of charge to the remaining 200 children after study completion.

### Vaccine Immunogenicity

When rabies vaccine is administered according to the recommended immunization schedule (days 0, 7, 21), nearly all subjects attain a protective titer. In two studies carried out in the United States in 101 subjects, all subjects attained antibody titers > 0.5 IU/ml by day 28. In studies carried out in Thailand (22 subjects), and in Croatia (25 subjects), all subjects achieved antibody titers above 0.5 IU/ml by day 14 (injections on days 0, 7, 21) (19-23). High antibody titers have also been demonstrated with off-label immunization with rabies vaccine. Among participants in England, Germany, France, and Belgium who received two doses one month apart, nearly all of the participants developed specific antibody; the geometric mean titer for the group was 10 IU (24-27). In a comparative study of two different rabies vaccines administered by the intramuscular route on either a 0, 7 and 21 day schedule or on a 0, 28 and 56 day schedule, the peak group GMT of rabies neutralizing antibody in international units (IU) was higher for both the chick embryo-basede vaccines (8.4 vs. 14.1 IU) and for the human diploid cell-based vaccine (13.7 vs. 19.3 IU) (21). The proposed immunization schedule of 0, 1, and 2 months is therefore expected to be highly successful in conferring protective immunity against rabies among the control participants.

### Vaccine Safety

Chiron’s PCEC rabies vaccine (purified chick embryo cell rabies vaccine; trademarked *RabAvert*® in the US and *Rabipur*® outside the US) is effective pre-exposure immunization and post-exposure treatment against rabies for all age groups. It is the most widely used high quality cell culture vaccine with more than 55 million doses administered in ~70 countries worldwide. This vaccine is WHO recommended and has been FDA approved since 1997. It is also licensed by MHRA, the UK regulatory agency, and is widely used in Kenya.

Aventis Pasteur’s *Imovax*® rabies vaccine is a human diploid cell vaccine (HDCV) whose safety and efficacy have been established in children. Local and/or mild systemic reactions may occur after injection, but these reactions are usually transient and do not contraindicate continuing immunization. In a study using five doses of HDCV, about 25% of recipients reported local reactions such as pain, erythema, and swelling or itching at the injection site (28). About 20% of recipients reported mild systemic reactions such as headache, nausea, abdominal pain, muscle aches, and dizziness (29). Two cases of neurologic illness resembling Guillan-Barre syndrome, a usually transient neuroparalytic illness, and a focal sub-acute central nervous system disorder temporally associated with HDCV, have been reported (30-32). Aventis Pasteur’s *Imovax*® rabies vaccine is FDA approved.

Systemic allergic reactions characterized by generalized urticaria and in some cases by arthralgia, angioedema, fever, nausea, and vomiting have been reported following administration of HDCV. These reactions, although uncommon in primary administrations, have been reported in up to 7% of persons receiving a booster dose (33).

In a comparative study in a pediatric population, both a HCDV and chick embryo-based rabies vaccines were found to have no statistically significant differences in adverse events (19). The study will plan to use the same rabies vaccine (*Rabipur*®) throughout the study, but in the event *Rabipur*® is not available, the *Imovax*® rabies vaccine will be used.

# JUSTIFICATION

## Malaria in Western Kenya

Malaria in western Kenya is holoendemic. Intense transmission occurs primarily by bites of the *Anopheles gambiae* mosquito. *P. falciparum* parasitemia is present in over 90% of malaria cases. *P. ovale* and *P. malariae*, which together constitute less than 10% of cases, are usually present in mixed infections with *P. falciparum.* Malaria transmission occurs all year but at a very high level during the two rainy seasons. The “long rainy season” of late March through May produces intense transmission from April through August; the “short rainy season” of October through December produces another, somewhat less intense, transmission season from November through January. The intensity of both transmission seasons can be predicted by the amount of rain seen in the preceding month and correlates with both the total population of female anopheline mosquitoes and the entomological inoculation rate (EIR, i.e., the number of infected mosquito bites per person per unit time). Cumulative malaria attack rates have been roughly 95% during the long rains and 75% during the short rains. The adult population of several villages not far from the study site has been the subject of several malaria chemotherapy and epidemiology studies. These studies typically demonstrate about 90% incidence of parasitemia over 12 weeks during a high transmission period. Approximately 25% of these infected adults will become symptomatic at some time during that period. Over the course of two disease seasons a large-scale longitudinal cohort project recently undertaken in Kisumu District (34) documented an 83% malaria parasite prevalence in the proposed study district and in the proposed study age groups (1 to 4 year-olds). The investigators of the present study conducted a longitudinal epidemiological study in 2003-2004 that indicates that monthly attack rates range from 20 to 55% in children aged 1 to 3 years in the proposed study area (unpublished data). As a conservative estimate for the purpose of calculating the sample size of this study, we have assumed that 50% of children will develop clinical malaria (as defined by the primary case definition) during the efficacy follow-up period of this study from study day 71 through study day 240. All individuals in this population are parasitemic multiple times over a lifetime. Undoubtedly, children in this population are malaria-exposed.

The Walter Reed Project (WRP) and the Kenya Medical Research Institute (KEMRI) have been involved in malaria research in western Kenya for many years. Their studies cover nearly every aspect of the disease: epidemiology, entomology, immunology, hospital-based treatment trials, and community-based studies of antimalarials. The WRP/KEMRI laboratories near Kisumu have served as the base for both phase I and II trials of candidate malaria vaccines and antimalarial drugs over the past decade. In spite of these research efforts, malaria infections in this area continue unabated and improved control strategies are required.

## Target Population

Children are the population with the highest rates of morbidity and mortality due to malaria, accounting for more than one million deaths annually in sub-Saharan Africa. Malaria is a significant cause of morbidity and mortality in both adults and children in western Kenya. In this area, the burden of malaria falls particularly hard on the younger age groups. Worldwide, the populations at risk for malaria include not only the infants, children, and adults in malaria-endemic regions, but also non-immune travelers to malarious areas including vacationers and deploying military personnel. A safe and effective vaccine that prevents infection, or even clinical symptoms of *P. falciparum* malaria, would be a milestone public health achievement and would become a mainstay in efforts to control this serious infectious disease around the world. The increasing prevalence of drug resistance in various malaria strains makes an effective vaccine an international priority in the struggle for control of this devastating disease.

The target population for this vaccine is children at risk for clinical disease (including severe disease) due to infection with *P. falciparum*. FMP1 can only be tested for proof of concept in this population, as there is no predictive animal model and no reliable challenge system to detect efficacy against clinical malaria. As described above, this vaccine has been tested in malaria‑naïve adults in the United States to establish safety and reactogenicity as well as to identify a dose for further evaluation. Subsequent evaluation in malaria-exposed Kenyan adults and children found it safe, well tolerated, and immunogenic in these populations. Three different doses and a control vaccine have been evaluated in 135 Kenyan children aged between 12 and 47 months (Mal-031). Data pertaining to 30 days post-dose 3 are described in section 3.5.2. This study aimed to assess long-term safety and immunogenicity. The AS02A adjuvant has been tested in combination with FMP1, as well as with the RTS,S vaccine in adults and children aged one year and older with prior (and ongoing) exposure to *P. falciparum* malaria. Both AS02A-containing vaccines have been found safe and well tolerated in adults and children.

The next logical step in the clinical development of FMP1/AS02A is to evaluate its efficacy in the pediatric population in a cautious, step-wise manner as described in this protocol. If this vaccine confers a significant delay in the onset of clinical episodes of malaria, it may be further developed either alone or with a pre-blood stage antigen as a combination vaccine, as indicated by the degree of efficacy demonstrated and by the results of a separate Phase IIb study. If the vaccine confers no reduction in clinical episodes of malaria, and there is a significant reduction in the episodes of parasitemia due to vaccine‑homologous *P. falciparum* strains, this vaccine may be developed in combination with a second MSP-1 vaccine based upon the FVO allele. If the vaccine confers no reduction in clinical episodes of malaria, and there is no reduction in the episodes of parasitemia due to vaccine‑homologous *P. falciparum* strains, the vaccine formulation will not be further developed.

# OBJECTIVES and HYPOTHESIS

The primary and secondary objectives pertain to children living in western Kenya and aged 12 to 47 months at the time of randomization.

## Primary

- To assess the efficacy of the FMP1/AS02A malaria vaccine on clinical episodes of *P. falciparum* malaria during the Efficacy Follow-up Period (EFP)

## Secondary

***Efficacy***

- To assess the efficacy of the FMP1/AS02A malaria vaccine against clinical episodes of *P. falciparum* malaria of differing severity during the EFP.

***Safety and Immunogenicity***

- To assess solicited adverse events occurring in the seven days following each dose of vaccine
- To assess unsolicited adverse events occurring in the 30 days following each dose of vaccine
- To assess serious adverse events occurring after the first dose of vaccine to the end of the EFP
- To assess the immunogenicity of the FMP1/AS02A malaria vaccine from the first dose of vaccine to the end of the EFP
- To assess the association between MSP-1 antibody titers and the subsequent risk of clinical malaria during the EFP

## Tertiary

The tertiary objectives pertain to the Addendum Efficacy Follow-up Period (AEFP).

***Safety and Immunogenicity***

- To assess the safety of the FMP1/AS02A malaria vaccine
- To assess the immunogenicity of the FMP1/AS02A malaria vaccine

***Efficacy and Exploratory***

- To assess the efficacy of the FMP1/AS02A malaria vaccine against clinical episodes of *P. falciparum* malaria
- To assess the biological effects of the FMP1/AS02A malaria vaccine

## Hypothesis

This trial is testing the null hypothesis that during the EFP the time to first clinical episode of *P. falciparum* malaria, according to the “Primary Case Definition”, is the same in the FMP1/AS02A and comparator vaccine arms.

Success in the context of evaluating this time is defined as a significant two-sided log‑rank test statistic (p-value <0.05), where time to first clinical episode is longer in the FMP1/AS02A arm than in the comparator arm.

# STUDY DESIGN and METHODOLOGY

## Overview

- Double-blind, randomized, controlled, phase IIb (pilot efficacy) field trial of a candidate antigen/adjuvant
- One study center, with 12 outlying (satellite) field stations
- Screening will be performed no more than 45 days prior to the first inoculation
- 400 subjects will be randomized 1:1 between two arms (FMP1/AS02A and rabies vaccine)
- Immunization schedule will be 0, 1, and 2 months for both study arms
- The four-week intervals between doses may be extended for up to two additional weeks if *temporary suspension* (see Section 6.9.1) is deemed advisable because of SAEs or other concerns
- All subjects will be randomized on the day of first vaccination
- Route of inoculation will be by IM injection into the left anterolateral thigh muscle (unless compelling reason for an alternate injection site is evident)
- Study duration will be approximately about 14 months per subject
- Seven-day follow-up period for solicited adverse events (five visits: vaccination day plus post-vaccination days 1, 2, 3, and 6)
- Thirty day follow-up period for unsolicited adverse events (vaccination day plus 29 subsequent days)
- Follow-up of serious adverse events (SAEs) for study duration
- Efficacy Follow-up Period (EFP): Starting 14 days after the third vaccination (Study Day 71), active case detection commences with visits approximately every 28 days to the WRP Kombewa clinic and terminates after six months (o/a Study Day 240): EFP = 169 days = six (28 day) months
- The primary study analysis for all endpoints will be done on the cleaned EFP database after a data-lock-point
- Addendum Efficacy Follow-up Period (AEFP): Starting with the end of the EFP (o/a Study Day 240), active case detection commences with visits approximately every 28 days to the WRP Kombewa clinic and terminates after 10 months (o/a Study Day 364); AEFP = 125 days = four and a half (28 day) months. This portion of the trial is partially unblinded.
- The study addendum analysis for all endpoints will be done on the AEFP database after a data-lock-point
- Malaria cases will be detected by active and passive means
- Active case detection will be through scheduled, facilitated visits by participants to the Kombewa clinic and scheduled, field worker visits to participants’ homes
- Passive case detection will take place by unscheduled, self-presentation of participants to the Kombewa Clinic
- At scheduled clinic visits, blood samples from all subjects will be taken to determine parasite density and hemoglobin levels. At home visits, only subjects with fever or history of fever within 24 hours (or other illness) will be transported to the clinic and sampled for detection of parasite densities and hemoglobin.
- The primary study analysis conducted at about month 10 (on the EFP data through SD 240) will be considered a “final” analysis; the study will continue an additional 4 months in a partially unblinded fashion (the AEFP data).

## Number of Subjects and Number of Study Arms

The study will randomize 400 subjects, irrespective of gender or age, who fulfill all enrollment criteria. The 400 subjects will be randomized 1:1 between the two arms (FMP1/AS02A and comparator).

## Study Center

### The Walter Reed Project Kombewa Clinic

The Walter Reed Project (WRP) Kombewa Clinic (WRP KC) is located in the village of Kombam (near Kombewa Town), in Kombewa Division, Kisumu District, Nyanza Province, Kenya. Kombewa Town is about 40 kilometers (40 minutes drive) west of Kisumu Town.

The WRP KC is located directly across the Kombewa-Maseno road (a murram road) from the Kombewa Sub-District Hospital (KSDH) where it is less than one kilometer north of the Kisumu-Bondo road (a macadamized road). (The KSDH, a Kenya Ministry of Health sub-district hospital, is an inpatient and outpatient facility; however, it is not to be utilized by study subjects.)

The WRP KC is readily accessible by foot or ground vehicle to all study subjects. It consists of a clinical laboratory equipped to carry out malaria diagnosis and basic clinical laboratory assays (such as measurement of serum chemistries and complete blood counts), a phlebotomy room, an outpatient facility that includes six examination/consultation rooms, a pharmacy, an active records room, and a records archive. Subject records and CRFs will be kept in locked cabinets in the latter two rooms. The facility has a dedicated data entry room, offices for clinical officers and CRCs, on-call rooms, an urgent treatment room, a four-bed observation suite, a washroom, a general store, and a kitchen with dining area.

The PI, associate investigators, and clinical officers (physician assistants) carry out clinical evaluations, including basic laboratory studies, at the WRP KC. Management of symptomatic malaria during this study will be undertaken here as detailed in Section 7.3. During the course of evaluation for malaria in the study subjects, other acute illnesses such as upper respiratory infections and other minor bacterial or viral infections may be uncovered. The pharmacy at the WRP KC will provide subjects with common over-the-counter analgesics such as paracetamol, as well as antibiotics (for the treatment of minor infections) as prescribed by the clinicians. The KC will be staffed at all times (24 hours a day, 7 days a week) by at least one clinical officer and one community nurse. A medical officer (physician) will be on site during working hours Monday through Friday. Additionally, a pediatrician will be on site on most working days and will always be available by telephone (See SOP 501.03: After Hours Care of Subjects).

This facility recently underwent expansion with the construction of a two-story annex block including new office spaces, more commodious general storage areas, a secure records archive room, meeting rooms, and a library.

### Field Stations and Follow-up Centers in Kombewa Division

To facilitate accessibility to the study participants, several field stations have been designated within Kombewa Division; all are located within one-mile radii of the homes of study subjects. Twelve field stations, of which three will be designated as field follow-up centers, will be utilized. Field stations and follow-up field centers are intended to be points of first contact for sick children; therefore, they are staffed 24 hours a day and are equipped to communicate with the WRP KC to summon transportation. (See Appendix D for details.)

### The New Nyanza Provincial General Hospital, Kisumu

The WRP KC does not have an inpatient facility or capability. Furthermore, blood transfusions cannot be administered there and a pediatrician is not usually present after hours or on weekends. If such procedures or expertise are required, or if hospital admission is deemed necessary, study personnel will transport the subject to the New Nyanza Provincial General Hospital in Kisumu. This hospital includes a 44-bed pediatric inpatient ward with an attached, dedicated laboratory staffed by WRP personnel. Inpatients, including any admitted study subjects, receive care overseen by Kenyan pediatricians. Three pediatricians are on staff (one of whom is employed by the WRP) and there are routine 24-hour nursing coverage, and blood transfusion and oxygen supplementation capabilities. In November or December 2004, the pediatric department plans to move to a new, more spacious building immediately adjacent to the existing hospital compound. This new facility will represent a significant upgrade with expansion to 64 beds and new laboratory, pharmacy, and outpatient departments. Limited laboratory support will also be available at the new WRP-Kisumu headquarters building adjacent to the new pediatric ward.

## Inclusion Criteria

- A healthy male or female child, 12 to 47 months of age on the day of screening
- Written informed consent obtained from at least one parent/guardian before study start
- Available to participate for the study duration (about 14 months)

## Exclusion Criteria

**The following criteria will be checked at the time of study entry. If any apply at the time of study entry, the subject will not be enrolled in the study. Additionally, parents will be queried on these criteria immediately before the second and third vaccinations, and any new information suggesting presence of one or more will serve as “elimination criteria” whereby subjects will have vaccination deferred pending further evaluation to determine whether to exclude them from further vaccinations.**

- Acute disease at the time of entry into the study that in the opinion of the investigator may pose a threat to the subject
- Axillary temperature  37.5C
- Respiratory rate  50 breaths per minute
- Serum ALT  50 IU/l (i.e., > 1.5 X ULN)
- Decreased renal function: serum creatinine levels > 92.2 mM/l (> 1.1 mg/dl)
- Significant anemia (Hgb < 8.0 g/dl)
- Thrombocytopenia (Platelets < 100,000 per mm3)
- Impaired immunity: (Absolute lymphocyte count [ALC] for 1 and 2 year olds < 2.5 x 103/mm3; for 3 year‑olds < 2.0 x 103/mm3)
- Homozygous sickle cell disease (Hgb SS)
- Malnutrition (Z score; Malnutrition = Weight for height < - 3 z-scores)
- Prior receipt of a rabies vaccine or any investigational vaccine
- Use of any investigational drug or vaccine other than the study vaccine within 30 days preceding the first dose of study vaccine, or planned use up to 30 days after the third dose
- Administration of chronic (defined as more than 14 days) immunosuppressants or other immune-modifying drugs within six months of vaccination. (For corticosteroids, this will mean prednisone, or equivalent, greater than or equal to 0.5 mg/kg/day. Inhaled and topical steroids are allowed)
- Administration or anticipated administration of a vaccine not foreseen by the study protocol within 30 days of the first dose of vaccine(s) with the exception of tetanus toxoid
- Previous vaccination with a vaccine containing MPL or QS21 (e.g., RTS,S/AS02A)
- Any confirmed or suspected immunosuppressive or immunodeficient condition, including human immunodeficiency virus (HIV) infection. (No HIV test will be performed as part of this study.)
- History of allergic reactions or anaphylaxis to immunizations or to any vaccine components, such as eggs
- History of surgical splenectomy
- Administration of immunoglobulins, blood transfusions, or any other blood products within the six months preceding the first dose of study vaccine or planned administration during the study period
- Simultaneous participation in any other clinical trial
- Acute or chronic cardiovascular, pulmonary, hepatic, or renal condition that in the opinion of the PI, may increase the risk to the subject from participating in the study
- Any other condition or circumstance that in the opinion of the investigator may pose a threat to the subject

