GSK Biologicals: GlaxoSmithKline Biologicals

GMT: Geometric Mean Titer

HBsAg: Hepatitis B surface antigen

HDCV: Human Diploid Cell Vaccine

Hgb: Hemoglobin

HLA: Human leukocyte antigen

hpf: High power field

HSPC: Human Subjects Protection Committee (PATH IRB)

HSRRB: Human Subjects Research Review Board (MRMC)

HURC: Human Use Research Committee (WRAIR)

IATA: International Air Transport Association

IAW: In accordance with

ICH: International Conference on Harmonization

ID: Identification

IEC: Independent Ethics Committee

IFA: Indirect fluorescent antibody

IFN-gamma: Interferon gamma

IL‑2: Interleukin 2

IM: Intramuscular; intramuscularly

IRB: Institutional Review Board

ITT: Intention-to-treat

IU: International units

IU/l: International units per liter

IV: Intravenous; intravenously

kDa: kiloDalton

KEMRI: Kenya Medical Research Institute

KSDH: Kombewa Sub-District Hospital

Ksh: Kenya shillings

LDH: Lactate dehydrogenase

LMM: Local Medical Monitor

MBF: Malaria blood film

MHRA: Medicines and Healthcare products Regulatory Agency (UK)

ml: Milliliter

mmol/l: Millimoles per liter

MPL: Monophosphoryl Lipid A

MSP-1: Merozoite surface protein 1

MVI: Malaria Vaccine Initiative

NANP: Repeat epitopes of the circumsporozoite protein

NA: Not applicable

ND: Not done

NNPGH: New Nyanza Provincial General Hospital, Kisumu, Kenya

NR: Not related

o/a On or about

OD: Optical density

ORP: Office of Research Protections, USAMRMC

PATH: Program for Appropriate Technology in Health

*P. falciparum*: *Plasmodium falciparum*

PB: Probable

PBMC: Peripheral blood mononuclear cells

PCR: Polymerase chain reaction

PCV: Packed [red blood] cell volume

PO: Administered orally

POC: Point of contact

PPD: Pharmaceutical Product Development

QA: Quality Assurance

QC: Quality Control

QS21: *Quillaja saponaria* 21 (saponin derivative)

RAP: Reporting and Analysis Plan

RCO: Registered Clinical Officer

RIA Radioimmunoassay

RNAE: Reportable non-serious adverse event

RR: Relative risk

RTS,S: A candidate pre-blood stage malaria vaccine antigen [See next 2 entries]

RTS: Fusion protein consisting of a circumsporozoite protein-based antigen and the hepatitis B surface antigen (HBsAg)

S: 226 amino acid polypeptide corresponding to the surface antigen of hepatitis B virus (adw serotype)

SAE: Serious adverse event

SB Biologicals/SB Bio: SmithKline Beecham Biologicals

SB62: An oil-in-water emulsion

SBAS2: SmithKline Beecham Adjuvant System 2

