Parents of subjects will provide a medical history (with special attention to any history of recurrent infections to suggest immune suppression, previous history of splenectomy, and prior vaccine reactions). Subjects will also undergo physical examination and routine standard laboratory screening tests, which include complete blood count (CBC), creatinine, and ALT. Hemoglobinopathies (sickle cell disease/trait, G6PD deficiency, and alpha-thalassemia) will also be screened. Subjects may be screened one additional time if re-screening after clinical intervention is determined to be necessary (e.g., treatment for malaria). Subjects will be excluded from participation if they meet any of the exclusion criteria (Section 6.5). Subjects excluded from this study because of significant abnormalities will be referred to the local health center for evaluation and treatment. All screening tests will be completed within 45 days prior to entry into the study; laboratory tests may be conducted at other times during the course of the trial if the investigator judges it necessary for the safety of the subject. All subjects randomized into the study will be identified and followed by SID number. All screening and follow-up diagnostic laboratory studies will be performed at the WRP KC laboratory. Information gathered during screening (medical history, physical examination, and laboratory analysis) will be recorded on the CRFs.

A photograph will be taken of each child who is screened, along with the parent/guardian, and stored securely in a computer at WRP KC. The investigator will randomize (see also Section 9.4) 400 eligible subjects who fulfill all the inclusion criteria and none of the exclusion criteria. A picture ID card of each eligible child and parent/guardian will be created using the stored photo, and the ID provided to each parent/guardian. The card will include contact details for study staff to facilitate documentation of medical care received outside the study health facilities. Copies of these pictures will also be kept in the subjects’ records to aid the study staff in confirmation of the child’s identification for future visits. The photos of subjects who are determined ineligible to participate will be deleted from the computer. CRFs will be filled in for all subjects enrolled in the study, and all data collected during the study will be recorded on the CRFs.

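### The creatinine exclusion gives two figures as one limit, but they do not convert into each other, so a narrow band of results is both excluded and eligible

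*Protocol*

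**What the plan says.** Protocol section 6.5 (Exclusion Criteria) lists, among the laboratory exclusions, "Decreased renal function: serum creatinine levels > 92.2 mM/l (> 1.1 mg/dl"). The bracket presents the second figure as a restatement of the first. The consequence at entry is firm: "If any apply at the time of study entry, the subject will not be enrolled in the study". Before the second and third doses the same section has parents asked about the criteria again. New information pointing to one of them leads to deferral of vaccination and further evaluation.

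Creatinine is measured routinely. Section 7.1.1 includes it in the "routine standard laboratory screening tests, which include complete blood count (CBC), creatinine, and ALT". Section 7.2 schedules it again at Visits 2, 7 and 12, where the eligibility criteria and earlier laboratory results are reviewed before each dose.

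The study has a single center (section 6.1: "One study center, with 12 outlying (satellite) field stations") and a single laboratory for this test (section 7.1.1: "All screening and follow-up diagnostic laboratory studies will be performed at the WRP KC laboratory"). No other section states a numeric creatinine limit. The unit in which the laboratory reports creatinine is not given.

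Section 12.2.2 requires subjects in the ATP cohort to satisfy the inclusion and exclusion criteria. Section 12.4.2 bases the primary analysis on that cohort.

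**The concern.** A numeric exclusion should give one answer for one result. Here it gives two, because the figures joined by the bracket are different concentrations of creatinine. For a result between them, the protocol does not tell staff whether the child may be enrolled.

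Two things depend on the answer. One is entry to the study, with the eligibility reviews before later doses. The other is membership of the ATP cohort: a child enrolled under one figure could later be classed as ineligible under the other, and so be moved out of the primary analysis population or recorded as an eligibility deviation. The printed unit raises a separate question, since taken literally it makes the first figure far too large to act as a limit.

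**Working it through.** **Inputs.** The two limits, 92.2 (printed unit mM/l) and 1.1 mg/dl, come from section 6.5. The molar mass of creatinine is not in the protocol. It is a physical constant, entered here as an assumption of 113.12 g/mol, with a range of 113.0 to 113.2 to show that its exact value does not matter.

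**Formula.** micromol/l = mg/dl × 10,000 / molar mass. At 113.12 g/mol the factor is 10,000 / 113.12 = 88.4.

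**Step 1: try to reproduce the stated equality, reading the unit as micromol/l.**
- 1.1 × 88.4 = 97.24 micromol/l (97.2 to 97.3 over the range of molar mass). The protocol has 92.2.
- 92.2 / 88.4 = 1.043 mg/dl (1.042 to 1.044 over the range). The protocol has 1.1.
- Gap: 97.24 − 92.2 = 5.04 micromol/l. The printed figure is 5.04 / 97.24 = 5.2% below the conversion of 1.1 mg/dl.

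The equality is not reproduced. It would need a factor of 92.2 / 1.1 = 83.8, that is, a molar mass of 10,000 / 83.8 = about 119.3 g/mol, well outside the range for creatinine.

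**Step 2: could rounding explain it?** To one decimal, 1.043 mg/dl becomes 1.0, not 1.1. The lowest value that rounds to 1.1 is 1.05 mg/dl, and 1.05 × 88.4 = 92.8 micromol/l, which is still above 92.2. Rounding does not explain the pair.

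**Step 3: the unit as printed (millimolar).** 92.2 mmol/l = 92,200 micromol/l, and 92,200 / 88.4 = about 1,043 mg/dl. That is about 948 times the bracketed 1.1 mg/dl, so the two figures are again unequal.

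**Step 4: which results are affected, if micromol/l is meant.**

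| Creatinine result | By > 92.2 micromol/l | By > 1.1 mg/dl |
| --- | --- | --- |
| up to 92.2 micromol/l (1.04 mg/dl) | eligible | eligible |
| above 92.2, up to 97.2 micromol/l (1.10 mg/dl) | excluded | eligible |
| above 97.2 micromol/l | excluded | excluded |

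A result of exactly 1.1 mg/dl falls in the middle row. If the laboratory reports mg/dl to one decimal (an assumption), every reading of 1.1 is in conflict.

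**The case against.** **The unit.** A reader might infer that the criterion is unusable as printed and would never exclude anyone. The document does not support that. The extracted text has lost micro signs elsewhere: the test-vaccine dose in the Summary appears in grams, and a reagent concentration in section 8.3.5 appears as 100 M. The abbreviation list also gives "mmol/l: Millimoles per liter", not mM/l. The prefix may therefore be an artefact. Against that, micro signs in this text are mostly dropped or kept rather than turned into the letter m, so an artefact is not proven either. Even if mM is as printed, the same line carries a workable mg/dl limit, and nothing shows that the laboratory reports in millimolar units. The unit is something to check; the inequality of the two figures stands either way.

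**Differences between sites.** A reader might also expect the ambiguity to be applied differently from site to site. With one center and one laboratory that cannot happen. What stands is that staff at the one center are not told which figure to apply.

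**Later doses.** It would be too strong to call this an automatic cut-off before doses 2 and 3. Section 6.5 provides for deferral and evaluation there, which is a judgement, although Visits 7 and 12 do review the criteria and earlier laboratory results.

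**Safety backstop.** Section 6.5 separately excludes a renal condition that the investigator thinks may increase risk, so renal safety does not hang on a band of 5 micromol/l. This is right, but it does not tell staff which number applies.

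**The analysis.** The screening decision precedes randomization, so the ambiguity at entry cannot differ by arm, and no affected child can be counted because no creatinine distribution is given. Both points stand and limit the weight of the matter. The screening form and procedure, which are not shown, may already carry a single working limit; the protocol line would still be wrong.

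**Conclusion.** The point holds as an error in one eligibility line. The two creatinine figures are presented as equivalent and are not, whichever unit was meant. Read as micromol/l, they differ by about 5 micromol/l (5.2%), and results above 1.04 and up to 1.10 mg/dl receive opposite answers. This rests only on the molar mass of creatinine, and the conclusion is unchanged across 113.0 to 113.2 g/mol. The claim of a thousandfold unit error is conditional on the prefix mM being as printed.

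The impact is probably small. Few children aged 12 to 47 months are likely to fall in so narrow a band, though this is an assumption that the protocol gives no data to test. Sample size, power and alpha are not affected. The case for correcting the line is that an operative threshold, which also feeds the ATP cohort, should have one meaning.

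**What to change.** Check the unit prefix against the source PDF. The sponsor's medical team should then reconcile the two figures and the unit into one limit, stated in the unit the study laboratory reports, with a correct conversion in brackets. Which limit is intended is for that team to decide, and none is proposed here. Use the same figure at screening, at the eligibility reviews before each dose (Visits 2, 7 and 12), and when judging eligibility for the ATP cohort. The cost is one line of the protocol, plus any case report form field or screening procedure that repeats the limit. Study operations and the statistical design do not change.
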